# Leukaemia in Pregnancy Study (LIPS)

## Synopsis

|                     |                                                                                                                           |
|---------------------|---------------------------------------------------------------------------------------------------------------------------|
| Full Protocol Title | A Prospective registry-based cohort study to monitor the diagnosis and management of acute leukaemia in pregnancy. |
| Sub Title           | Acute leukaemia in pregnancy cohort study.                                                                         |
| Protocol Version    | 1.0
14th June 2019                                                                                  |
| HHTU Ref            | P006                                                                                                               |
| IRAS ID             | 238879                                                                                                             |
| REC                 | 19/CBS/3662                                                                                                        |
| Clinicaltrials.gov  | Tbc                                                                                                                |
| Study Design        | Registry based cohort study                                                                                        |
| Study Parameters    | Diagnosis information
Pregnancy information
Delivery information
Follow-up information                 |
| Authorised By       | [name]                                                                                                       |
|                     |                                                                                                                           |

---

## ABBREVIATIONS

### Definition of terms

|       |                                                |
|-------|------------------------------------------------|
| AL    | Acute leukaemia                                |
| AML   | Acute myeloid leukaemia                        |
| ALL   | Acute lymphoblastic leukaemia                  |
| ART   | Assisted reproductive technology               |
| ATRA  | All- trans -retinoic acid               |
| BCSH  | British Committee for Standards in Haematology |
| COSD  | Cancer Outcomes and Services Dataset           |
| eCRF  | Electronic case report form                    |
| HEY   | Hull and East Yorkshire Hospitals NHS Trust    |
| HHTU  | Hull Health Trials Unit                        |
| HSCT  | Haematopoietic stem cell transplantation       |
| MDS   | Myelodysplasia                                 |
| POF   | Premature ovarian failure                      |
| RCC   | REDCap cloud                                   |
| TMG   | Trial Management Group                         |
| UKOSS | UK Obstetric Surveillance System               |
| UOH   | University of Hull                             |

## Protocol amendments since Version 1.0

None

---

## STUDY SUMMARY

Acute leukaemia (AL) is an aggressive but potentially curable cancer that can affect women of childbearing age. When a pregnancy is complicated by a diagnosis of AL, clinicians face a complex dilemma: to balance risking the mother's survival through delaying treatment, against the potential harm to the foetus through exposure to cancer drugs. Reports suggest that, providing the first trimester is avoided, successful treatment of AL during pregnancy is possible, and considered safe. However, there is currently no standard approach to treatment of these women.

This observational study aims to monitor and record the current treatment and outcomes of patients diagnosed with acute leukaemia during or prior to pregnancy. Patients will receive the treatment recommended by their doctor, the study will not alter the treatment pathway of participants. This study will establish a new research database of Leukaemia in Pregnancy, initially collecting data from cases in the past ten years, and any new cases that are diagnosed during the current funding period.

The initial planned analyses from this dataset will enable more robust, evidence-based recommendations to be made on how to monitor and manage these patients, and will add value to and improve the existing British Committee for Standards in Haematology (BCSH) guidelines, which were largely derived from expert opinion. This should enable healthcare professionals to have greater confidence in managing these patients, leading to a more standardised approach to providing high quality care. The study will benefit NHS Trusts and patients across the UK through more informed clinical decision making with regards to the care they receive. It will also provide an important data resource which researchers can apply to use in further analyses, with plans to continue data collection if further funding is obtained.

---

# 1. INTRODUCTION

Acute leukaemia (AL) is an aggressive, but potentially curable, neoplasm of haematopoietic origin, encompassing both acute myeloid leukaemia (AML; approximately two-thirds of cases) and acute lymphoblastic leukaemia (ALL) subtypes [1-3]. Both AML and ALL present in all ages, and can therefore affect women of childbearing age; AL may therefore be diagnosed during the course of a pregnancy, or a woman diagnosed and treated for AL may wish to have children at a later date.

## Background

The true incidence of AL in pregnancy is not well known, but it is estimated to affect approximately 1 in 75,000 to 100,000 pregnancies [4]. Despite this rarity, AL is one of the most frequent malignant diseases observed during pregnancy [5]. When a pregnancy is complicated by a diagnosis of AL, this poses a unique clinical dilemma, with conflict between the risk of prognostic detriment incurred to the mother through delaying treatment and the potential for harm to the foetus as a result of exposure to chemotherapeutic drugs. Clinicians face very difficult decisions in planning the treatment of these patients; their management requires a specialised, cooperative multidisciplinary approach by consultant haematologists, obstetricians, anaesthetists and neonatologists.

The challenge of treating AL during pregnancy is greater than for solid tumours or lymphoma as its markedly aggressive nature necessitates higher doses of induction chemotherapy [6]. If left untreated, both mother and baby will likely die; however, evidence to date suggests that successful treatment of AL is both feasible and safe with the foetus *in utero* [7], with reported complete remission rates of up to 80% after standard chemotherapy [8, 9]. Furthermore, there are several reports of the successful use of all-*trans*-retinoic acid (ATRA) therapy in combination with conventional chemotherapy for the treatment of acute promyelocytic leukaemia (APL) [10-13]. Additionally, leukaemia treated to remission at the time of delivery has been associated with decreased maternal and foetal morbidity and mortality compared with untreated leukaemia [9].

The number of women who have previously been treated for AL but go on to become pregnant has not been studied. Accumulating evidence indicates that ovarian reserve can be adversely affected by chemotherapy in cancer patients [14], and the intensive cytotoxic therapy and sometimes craniospinal or total body irradiation required for the treatment of AL, can result in post-treatment premature ovarian failure (POF), with a high risk of induction of early menopause and infertility [15, 16]. Preconditioning regimens for haematopoietic stem cell transplantation (HSCT) comprising alkylating agents and/or irradiation carry a particularly high risk for germ cell injury, gonadal dysfunction and infertility [17] and, post-HSCT, these women face an increased risk of spontaneous abortions and miscarriages, pre-term delivery and low birth weight babies. Unfortunately, due to the aggressive nature of the disease, a lower intensity chemotherapy regimen cannot be considered in these women and, as treatment must be started immediately after diagnosis, their pre-treatment options to preserve fertility (e.g. embryo, oocyte or ovarian tissue cryopreservation)

are much reduced. However, fertility and parenthood remain important quality of life issues for cancer survivors of childbearing age [16] and so cannot be ignored.

Despite this, there have been reports of successful pregnancies following treatment of AML, APL and ALL, both with and without the use of assisted reproductive technology (ART) [18], and it appears that the likelihood of ovarian failure (and the chances of subsequent recovery of ovarian function) depend on a variety of factors including patient age, type of cytotoxic agent used, and the cumulative chemotherapy dose [15]. There is also a crucial need to gather data on the incidence of viable pregnancies among women who have previously received treatment for AL in order to better advise on the initial care of a young woman diagnosed with AL, as well as the management of any future pregnancies.

There is no standard approach for the treatment of AL during pregnancy and the effects on fertility post treatment are not fully known. This clinical dilemma also includes obstetric uncertainties such as mode and timing of delivery, use or not of neuraxial anaesthesia/general anaesthesia, optimisation of blood counts pre-delivery. It therefore remains an important need to collect data about the treatment and outcomes of these individuals. Current therapeutic approaches may be highly variable, and may differ from those used routinely to treat the disease in non-pregnant patients. Given the rarity of AL in pregnancy, there is a relative paucity of evidence concerning its diagnosis and management, currently limited to individual case reports, very small retrospective case series and reviews pertaining to only a small number of patients.

Performing large trials on these patients is virtually impossible, not only in practical terms because of the relatively small number of prospective cases, but also due to the ethical concerns around the potential exposure of fetuses to cytotoxic agents, and therefore few institutions are able to build sufficient clinical experience with this scenario.

The current British Committee for Standards in Haematology (BCSH) guidelines [19], specifically address and make recommendations on diagnosis and management issues associated with AML during pregnancy. However, although of great value, only low-quality evidence could be obtained to inform the guidelines and many of the recommendations were derived from expert opinion. Furthermore, for ALL scant available data at present regarding its treatment during pregnancy has so far precluded the establishment of firm recommendations [20]. With the prevalence of cancer during pregnancy expected to rise due to an increase in average age at pregnancy [21], there is a real need to consolidate firm recommendations on the effective therapeutic management of these patients.

The Swedish Acute Leukaemia Registry and Danish National Acute Leukaemia Registry both gather data on diagnosis, treatment response and survival [22, 23]; however, pregnancy in these patients is not studied in any great detail. For the NHS in England, the national standard for reporting cancer is the Cancer Outcomes and Services Dataset (COSD) [24], while the Systemic Anti-Cancer Therapy Dataset [25] collects data on the management of patients receiving cancer chemotherapy. However, these do not provide UK-wide coverage, and are also not designed to

capture the specifics relating to pregnancy. The UK Obstetric Surveillance System (UKOSS), established by the National Perinatal Epidemiology Unit at the University of Oxford, is a unique national reporting system for uncommon disorders of pregnancy [26], but does not include the required long-term patient follow-up in its studies and only collects prospective cases.

The purpose of this study is to capture both retrospective and prospective epidemiological, management and outcome data, to enable a more comprehensive assessment of the risks of cytotoxic therapy in this setting. The results will start to address the scarcity of evidence on the long-term effects of chemotherapy to a foetus exposed *in utero* and to a pregnancy conceived after completion of AL treatment. The study will serve a dual purpose: both as a supportive care study to monitor pregnancies during AL treatment, and also as a late effects study to report on the feasibility of viable pregnancies post-treatment. It will further provide a more accurate reflection of the management of AL during pregnancy, thereby allowing us to assess the impact of the introduction of the BCSH guidelines. It is intended to serve as a valuable resource to amalgamate and strengthen existing expertise on the topic, establishing a Leukaemia in Pregnancy research database. Initial planned analyses will inform more robust, conclusive, evidence-based patient management recommendations to better direct counselling and management of these patients, and to inform future patterns of care.

---

## 2. AIMS AND OBJECTIVES

This study aims to establish a research database to collect information about women who have a diagnosis of acute leukaemia (AL) or high-risk myelodysplasia (MDS) in pregnancy, or who have conceived after receiving treatment for either AL or high-risk MDS. Initial planned analyses will add to the evidence base, and the database will provide a source of data for future studies.

### Primary outcome:

- To ascertain the outcomes of mothers and babies treated for AL or high-risk MDS during or prior to pregnancy.

### Secondary outcomes:

- To document the current management practices for patients diagnosed with AL or high-risk MDS during pregnancy or who become pregnant after receiving therapy.
- To study the safety of any medication used and to identify toxicities to mothers and babies related to any chemotherapy given.
- To establish a Leukaemia in Pregnancy research database

---

### 3. DATA SYSTEMS

Data will be hosted and managed by the Hull Health Trials Unit (HHTU) using their secure online data capture system RedCap Cloud (RCC) and BOX Governance file storage system. HHTU hold a NHS Digital Data Security and Protection Toolkit covering these information systems.

Box is a cloud content management system which is ISO27001/ISO27018 certified and holds SOC1,2 and 3 reports. Box use IBM servers, the primary data centre is London with a backup in Frankfurt.

RCC is a cloud based EDC system provided by nPhase. Data is stored on dedicated RCC hardware in EU data centres (including real-time backup) managed by Amazon Web Services to industry standards outlined in ISO 27001, PCI DSS, SOC 1 - 3, FISMA, CIS, CSA, NIST and UK Cloud Security Principles. Data is encrypted at rest and in transit. RCC deliver compliance to HIPAA, CFR Part 11, and EMEA Annex 11.

Both of these systems have been through rigorous Information Governance and Security assessments during the University of Hull's procurement process.

---

### 4. STUDY DESIGN

A registry-based cohort study to identify and collect data on all women receiving a diagnosis of AL or high-risk myelodysplastic syndrome (MDS), and all women with a history of AL or high-risk MDS who fall pregnant within the study period. This is an observational study, and patients will receive usual care as determined by their Loco-regional multidisciplinary team.

In the UK, only hospitals with high intensity units treat AML and ALL, and therefore only these centres will be targeted for case identification. We aim to approach all consultant haematologists involved in the care of a woman diagnosed with AL during pregnancy, and request that they report all known cases, creating a national dataset.

For prospective cases, women will be identified at diagnosis and tracked throughout their pregnancy to allow comparison of the respective outcomes for both mother and neonate. There will be additional follow-up points at 2 and 4 years (as permitted within the duration of the study), to accurately document the subsequent outcomes of both mothers and neonates; 2 years is where the most incidences of relapse occur, and 4 years is considered decisive with regards to remission. In addition, consultant haematologists across the UK will be asked to provide retrospective data on any cases occurring since August 2009 (both pre- and post-introduction of the 2015 BCSH guidelines), to gain an overview of current and past approaches to patient management, and to serve as comparators to assess the current and future impact of the BCSH guidelines.

The methodology of data collection will be similar to that employed by the UK Obstetric Surveillance System (UKOSS) [27], which has received the approval of the London Multi-Centre Research

Ethics Committee (reference 04/MRE02/45). Within UKOSS, descriptive, case-control and anonymised cohort studies are conducted through a prospective, monthly case-collection scheme. Each month UKOSS sends electronic requests to nominated individuals at each Hospital site, inviting them to submit a case report. Where appropriate, more detailed data collection forms are then issued via post for completion.

We will use similar methodology to collect both retrospective and prospective data. Consultant haematologists will receive a reminder every 3 months via email. The email will include a link to the HHTU electronic data capture system where they will be able to submit any cases, either current or historical, into the study database. Once a case is identified, current patients or historical cases where the patient is still in active follow up or in regular contact with the clinical care team will be approached for consent. In historical cases where the patient is no longer in active follow-up or in regular contact with the clinical care team, cases will be processed without consent subject to the relevant approvals being gained.

Each patient entered onto the database will be designated a unique study identification number, generated automatically by the data capture system. Different case report forms will be activated accordingly as data is entered onto the system. Data will be entered directly into the database by the consultant haematologist through reference to medical records only, there will be no direct contact with patients. All data will be reported anonymously using the patient ID.

During the study set-up phase, consultant haematologists will be asked to provide an estimate of the number of cases encountered in the past ten years to enable a HHTU Trial Manager to monitor overall data collection rates. Email reminders will be issued, or the Local Clinical Research Team will be contacted by telephone, in order to minimise loss to follow-up. If a consultant haematologist is unwilling or too busy to provide a response, efforts will be made to identify an alternative suitable reporting individual at that site (e.g. an obstetrician) who would be part of the usual care team.

---

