In order to maintain patient confidentiality, no addresses, postcodes, hospital or NHS numbers will be collected within the database. However, data will be linked in an anonymised format in order for participating sites to obtain further information from clinical records and to complete follow-up data collection forms at the appropriate time points. Individual sites contributing data will maintain a code sheet linking the patient study number to identifiable data, which they will store according to their local data protection policies.

More detailed eCRFs relate to the initial AL diagnosis for those patients diagnosed during pregnancy, or prior to pregnancy. Further eCRFs will then be completed at appropriate time points to allow data to be subsequently collected from each patient upon completion of therapy, after the expected delivery date (if not already captured within the 'completion of therapy' time-point) and then for 2 defined follow-up data collections. For patients with previous AL, pregnancy, delivery and follow-up information will be collected. The specific data to be collected will enable effective assessment of current management practices for these patients and will allow us to ascertain the rate of successful outcomes of both mothers and neonates, as well as to determine the safety and related toxicities of any chemotherapy administered.

---

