## 7. STATISTICS

The statistical analysis will be mostly descriptive, and the resulting report will detail current and past management regimens and complications for AL in pregnancy, and will examine the impact of the introduction of the BCSH guidelines. Providing a satisfactory response rate is achieved, incidence data will be included, calculated with 95% confidence intervals. The LIPS Statistical Analysis Plan detailing the statistical analyses will be produced and signed off prior to the data analysis.

An interim report will be produced for funder review and research purpose. Final analysis will be carried out after the completion of data collection of all prospective cases. A summary report will be generated and circulated to all participating centres in order to evaluate the success of the study.

As the number of prospective cases expected is fairly low (approximately 10 cases per year), no strict sample size calculation has been made. The objective is to collect the maximum number of cases to improve the power of the study.

---

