Following the planned completion of data collection and analysis funded by the Bloodwise grant, HHTU will develop and manage a process for request to access the data by other researchers. A data management panel, including if possible a PPI representative will be established to review and approve requests. There will be a requirement for researchers to read, agree and sign a data sharing agreement, HHTU acceptable use policies and SOPs prior to release of data. Anonymised data sets for release will be produced according to HHTU SOPs.

The study team will apply for further funding for maintenance and ongoing collection of data beyond the end of the current funding period.

---

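### Prospective women who are between scheduled forms at data lock add no survivor follow-up after their last form; one status record at lock would recover it

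*Protocol*

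**What the plan says.** - **Entry.** The Study Summary takes in past cases and "any new cases that are diagnosed during the current funding period". No earlier closing date for entry is given.
- **End of collection.** Section 10 describes what happens "Following the planned completion of data collection and analysis funded by the Bloodwise grant", so both activities end under that grant. Anything later depends on money not yet secured: "The study team will apply for further funding for maintenance and ongoing collection of data beyond the end of the current funding period".
- **Follow-up points.** Section 4 plans "additional follow-up points at 2 and 4 years (as permitted within the duration of the study), to accurately document the subsequent outcomes". It explains the choice of times: "2 years is where the most incidences of relapse occur, and 4 years is considered decisive with regards to remission". The time origin of these points is not stated.
- **Forms.** Section 6 lists, after the diagnosis forms, collection at completion of therapy, after the expected delivery date, and at two follow-ups. It expects that these data "will allow us to ascertain the rate of successful outcomes of both mothers and neonates". Section 9 lists the date of death of mother or child among the items held.
- **Final analysis.** Section 7 states: "Final analysis will be carried out after the completion of data collection of all prospective cases". It does not say what makes a prospective case complete. It expects "approximately 10 cases per year".

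**The concern.** Entry that stays open until the grant ends, with collection ending under the same grant, leaves the latest entrants with the shortest follow-up. The clause limiting follow-up to the study's duration admits this but does not deal with it. In the text, nothing is recorded about a living woman between her last scheduled form and lock. A woman locked at 3.9 years is known alive only to her 2-year form, and one locked at 1.9 years only to her delivery or end-of-therapy form. A death in the same interval can be entered with its date.

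The outcomes of mothers and babies are the primary outcome, and section 4 treats 4 years as the decisive time for remission. Prospective cases are few, so survivor time that is available in the clinical record but never collected is a real loss. Analysis methods can handle unequal follow-up, but they cannot supply a date last known alive that no form asked for. Once the grant has ended, that date is hard to recover.

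**Working it through.** The protocol gives no study length, sample size or follow-up share, so there is no figure of its own to reproduce.

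**Inputs**
- From the protocol: 10 prospective cases a year (section 7); entry through the funding period (Study Summary); collection ending under the same grant (section 10); follow-up at 2 and 4 years (section 4); form schedule (section 6).
- Assumed: study length T; even entry up to lock at T; follow-up times counted from entry; constant hazard with 50% four-year mortality (30% as a second case); delivery form at 0.4 years. None of these is in the protocol.

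**Step 1. Share reaching each point.** The share reaching h years is max(0, T − h)/T.

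| T (years) | Women entered | Reach 2 years | Reach 4 years |
|---|---|---|---|
| 3 | 30 | 10 (33%) | 0 |
| 4 | 40 | 20 (50%) | 0 |
| 5 | 50 | 30 (60%) | 10 (20%) |
| 6 | 60 | 40 (67%) | 20 (33%) |
| 8 | 80 | 60 (75%) | 40 (50%) |

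The share is below one half when T < 2h, that is, T < 8 for the 4-year point and T < 4 for the 2-year point.

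**Step 2. Person-years with a status record at lock (T = 5, 50% mortality).** The hazard is λ = ln 2 / 4 = 0.1733 per year. A woman with potential follow-up f contributes on average (1 − e^(−λf))/λ. Over all entrants this is 10 × [5/λ − (1 − e^(−5λ))/λ²] = 10 × (28.85 − 19.30) = 95.5. If follow-up is cut at 4 years, it is 10 × [4/λ − 0.5/λ² + 0.5/λ] = 10 × (23.08 − 16.65 + 2.89) = 93.2.

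**Step 3. Person-years on the fixed schedule, same assumptions.**
- *Low end:* only the 2- and 4-year forms count, and nothing is known after the last one. Entrants with 2 to 4 years of potential follow-up (two years of entry) contribute (1 − e^(−2λ))/λ = 1.690 each. Those with 4 to 5 years (one year of entry) contribute 0.5/λ = 2.885 each. The total is 10 × (2 × 1.690 + 2.885) = 62.7.
- *High end:* a delivery form at 0.4 years is added, and deaths are dated whenever they occur. The loss is then survivor time after the last form L, which is 10 × ∫(f − L)e^(−λf)df. Over the intervals 0–0.4, 0.4–2, 2–4 and 4–5 years it is 10 × (0.076 + 0.995 + 1.126 + 0.223) = 24.2. The total is 95.5 − 24.2 = 71.3.

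About 63 to 71 person-years therefore compares with 93 to 96.

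**Step 4. Sensitivity.** With 30% four-year mortality, the same calculation gives about 70 to 78 against 105 to 108. If an end-of-therapy form also fell at 1 year, the high end for 50% mortality would rise from 71 to about 76. The gap narrows but does not close.

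**The case against.** **The passages contradict each other.** A reader might infer that they cannot all hold. The text does not require this. The duration clause in section 4 can govern the two follow-ups in section 6, and completion in section 7 can mean all the collection that this clause allows. The protocol also discloses the limit by planning to seek further funding. This stands, so the point is an undefined term and a gap in the data collected, not a contradiction.

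**Most women miss both points.** The protocol does not support this for the 2-year point, because at 5 years' length 30 of 50 reach it.

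**The reported rate will be biased.** For example, if the true 2-year event-free rate were 50%, counting every entrant not yet known to have failed as a success would give 65% at T = 3 and 59% at T = 5. But section 6 gives the rate no horizon or denominator, and section 7 leaves the analyses to the statistical analysis plan. Censoring, competing risks and denominators belong there, and their absence from the protocol is no fault.

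**Women may be undelivered at lock.** If diagnosis is spread evenly over 40 weeks, a hard lock would leave about 10 × 20/52 = 3.8 pregnancies open. This is only a possibility. Section 6 plans a form after the expected delivery date, and section 7 waits for prospective collection to be complete.

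**The form content is not visible.** The section 6 figure is not shown, and section 10 puts variables and events in a separate database specification. A lock record may exist there, and the protocol does not say how deaths between forms are captured. The working covers both ways of treating such deaths.

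**The mortality assumption is crude.** The 10 cases a year are not split between women diagnosed in pregnancy and women conceiving after earlier treatment, whose risks may differ. This stands, so the person-year figures are illustrations.

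**Retrospective cases are little affected.** With even occurrence from August 2009 to June 2019 (9.83 years), (9.83 − 4)/9.83 = 59% already had 4 years by June 2019. The point is limited to prospective cases.

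**Conclusion.** The point holds as an inexpensive improvement to data collection. Open entry and a shared end of funding truncate prospective follow-up. For any study length under 8 years, most prospective women will not reach the 4-year point; the corresponding limit for the 2-year point is 4 years. On the forms listed in section 6, women between points at lock lose their survivor time after the last form. At an assumed 5 years and 50% four-year mortality, that loss is roughly a quarter to a third of the obtainable maternal person-years: (95.5 − 71.3)/95.5 = 25% at the high end of Step 3 and (95.5 − 62.7)/95.5 = 34% at the low end. The size rests on even entry, constant hazard and an assumed study length. The direction follows from the form schedule, provided no lock record exists elsewhere. No conclusion is drawn about bias in the reported rate.

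**What to change.** 1. In sections 4 and 6, add one status entry at data lock for every prospective mother and child, completed from the medical record: alive or dead, relapse, date last known alive, and pregnancy outcome if delivered.
2. In section 7, define completion of prospective data collection as at least the post-delivery form plus this lock record for every prospective case, and make this consistent with the timing in section 10. It follows that lock must come after the last expected delivery date, or entry must close early enough before lock.

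With these data, 2- and 4-year outcomes can be estimated with censoring at lock, by whatever method the statistical analysis plan sets.

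**Cost.** One short extra entry per prospective case, about 50 in all at 5 years, with no patient contact or extra visits because sites already work from records. The 4-year intervals will be visibly wide, which reflects the information available.
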